### Study design

2.1

The study protocol follows the standard protocol items: recommendation for interventional trials (SPIRIT) guidelines.^[20]^ This is a prospective, single-central, non-randomized, non-blinded, phase I/II clinical controlled trial. All eligible patients will be assigned into 2 comparison groups (the L-ISR group and the L-ELAPE group) according to their own will after detailed preoperative conversations. The flow diagram of this trial is shown in Figure 1. Our trial started from September 2018 in West China Hospital of Sichuan University and is expected to end in 2021.

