### Outcome measures

2.4

The primary outcomes of this trial are to be scores of European Organization for Research and Treatment of Cancer QoL questionnaire-core 30 (QLQ-C30), QoL questionnaire-colorectum 29 (QLQ-CR29), Wexner Incontinence Score, International Prostate Symptom Score (for male), International Index of Erectile Function-5 (for male) and Female Sexual Function Index (for female). General QoL is assessed basically by scores of European Organization for Research and Treatment of Cancer QLQ-C30 version 3.0^[24]^ and QLQ-CR29.^[25]^ Defecation functions (daily defecation, frequency, urgency, incontinence, differentiation between defecation and gas emission, pad use, antidiarrheal drug use, and the presence or absence of erosion around the anus) are evaluated by the Wexner Incontinence Score.^[26]^ Sexual function for men and women is assessed by using the International Index of Erectile Function-5^[27]^ and Female Sexual Function Index,^[28]^ respectively. Urinary function is assessed by using the International Prostate Symptom Score^[29]^ for men and color ultrasonography of residual urine volume for all.

The secondary outcomes include incomplete CRM rate, 3-year local recurrence, 3-year disease-free survival, 3-year overall survival, and other surgical outcomes. Incomplete CRM is defined as tumor within 1 mm from closest mesorectal fascia, or within 1 mm from closest levator muscle, or invasion into or beyond the insphincteric plane. Local recurrence is defined as recurrent disease in the pelvis or at the incision. Disease-free survival is defined as the time of surgery to recurrence or end of follow-up. Overall survival is defined as the time of surgery to the date of death from any cause or the end of follow-up. Surgical outcomes include operation time, intraoperative blood loss, temporary stoma, intraoperative perforation, time to first flatus, time to liquid diet intake, postoperative hospitalization days, postoperative complications, incidence of urinary retention, and postoperative mortality in 30 days.

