### Sample size

2.5

This is a non-inferiority verification study with QoL and efficacy as the main index. In the pilot study, incomplete CRM rate was 6.1% (2 out of 33 patients) in the L-ELAPE group. Based on the previous studies, we assume that the rate of incomplete CRM in the L-ISR group was 8.1% which was the average value in the meta-analysis.^[30]^ The adjusted formula below is used to calculate the sample size^[31]^ (Fig. 2). The “Pe” and “Pc” are the rates of incomplete CRM of the experiment group and the control group, respectively. The “k” represents the ratio of 2 groups’ sample sizes which equals 1 in this trial and “p” represents the joint probability. Setting type I error probability **α** = 0.025, type II error probability **β** = 0.2, the sample size required for each group is 72 cases. Furthermore, we assume that there will be a 20% dropout rate. Therefore, at least 159 patients are needed in this specific trial.

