### Randomization and blinding

2.6

Due to the specificity and ethics, it is unlikely that any surgical center around the world would randomize patients to receive either L-ISR or L-ELAPE due to a lack of equipoise regarding the requirement for each operation in any particular patient. Direct comparison by a randomized controlled trial of the 2 procedures is currently virtually impossible. This trial allows the surgeons and outcome assessors to be aware of the whole assignment and all eligible patients will be informed of the treatment in detail on admission to hospital. However, statisticians responsible for the final analyses will be blinded.

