### Data collection, management, and statistical analyses

2.7

For purpose of acquiring high-quality monitoring, we plan to employ several professional clinical investigators to collect and manage the data of all participants during entire trial performing. A Case Report Form (CRF) is designed for each participant to document their data. And we will upload the data of all participants to Research Manager (ResMan), an Electronic Data Capture (EDC) system, and the individual patient data (IPD) will be publicly accessed via Chinese Clinical Trial Registry (ChiCTR.org) within 3 years after completion of this trial.

SPSS for Windows, version 22.0 (IBM Corp, Armonk, NY) will be used for statistical analysis. The data are presented as the mean value **±** standard deviation for continuous variables and as a number for categorical variables. The difference of categorical data and continuous data will be compared with Student *t* test and chi-square test between the 2 groups, respectively. The Kaplan–Meier estimate will be used to analyze survival and fit survival curves. The multiple factor analysis will be performed by using Cox regression model.

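### Patients choose their operation, but the QoL scores and the incomplete CRM rate are compared without any stated adjustment for confounding by indication

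*Protocol article*

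**What the plan says.** - **Allocation.** Section 2.1 (Study design) has patients join a group "according to their own will after detailed preoperative conversations". The abstract says the same.
- **Reason for not randomising.** Section 2.6 (Randomization and blinding) says that centres would be unlikely to randomise "due to a lack of equipoise regarding the requirement for each operation in any particular patient". The same section blinds the statisticians.
- **Outcomes.** Under section 2.4 (Outcome measures) the primary outcomes are questionnaire scores: QLQ-C30, QLQ-CR29, Wexner, IPSS, IIEF-5 and FSFI. Incomplete CRM is listed as secondary: "The secondary outcomes include incomplete CRM rate". Section 2.5 (Sample size) nevertheless uses it to size the trial and states: "This is a non-inferiority verification study with QoL and efficacy as the main index".
- **Analysis.** Section 2.7 states: "The difference of categorical data and continuous data will be compared with Student *t* test and chi-square test between the 2 groups, respectively". It then names Kaplan–Meier for survival and ends with: "The multiple factor analysis will be performed by using Cox regression model".

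Read literally, the word order in section 2.7 pairs the t test with categorical data and chi-square with continuous data. That is a separate slip. The intended pairing is evident, and neither reading supplies adjustment.

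**The concern.** When the operation is chosen and not randomised, a crude difference between groups combines the effect of surgery with the reasons for the choice. Section 2.6 itself ties the operation to the individual patient, so this possibility follows from the protocol's own account of its design.

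The one multivariable tool needs a time-to-event outcome. It can adjust disease-free survival, overall survival and time to local recurrence. It cannot be applied to a questionnaire score or to a yes/no margin result at resection. Adjustment is therefore available for some secondary outcomes, but not for the primary outcomes or for the outcome that sets the sample size.

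The conclusion on offer is non-inferiority, meant to inform treatment guidelines. Selection alone could create or hide such a result. Blinding the statisticians does not help, because the imbalance would lie in the data.

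**Working it through.** **Plan figures (section 2.5)**
- L-ELAPE incomplete CRM: 2/33 = 6.1%. L-ISR assumed: 8.1%. Difference: 8.1 − 6.1 = 2.0 points. Mean: (8.1 + 6.1)/2 = 7.1%.
- Expected events at 72 per group: 72 × 0.081 + 72 × 0.061 = 5.8 + 4.4 = 10.2.

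The documents give no data on imbalance between the groups, so everything below is assumed.

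**CRM: one binary factor, no effect of surgery**

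Let r₀ be the risk without the factor, RR its risk ratio and p its prevalence. The crude rate in a group is r₀ × [(1 − p) + p × RR]. With RR = 3 and prevalences of 15% and 45%, the multipliers are 0.85 + 0.45 = 1.30 and 0.55 + 1.35 = 1.90. The false difference is therefore 0.60 × r₀.

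| Anchor | r₀ | Crude rates | False difference |
|---|---|---|---|
| L-ELAPE has the 45% and a rate of 6.1% | 6.1/1.90 = 3.2% | 4.2% and 6.1% | 1.9 points |
| Mean of the two groups is 7.1% | 7.1/1.60 = 4.4% | 5.8% and 8.4% | 2.7 points |
| Risk without the factor is 6% | 6.0% | 7.8% and 11.4% | 3.6 points |

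The third row gives a mean of 9.6%, above the plan's 7.1%, so it is the upper end of the range.

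The sign depends on which group carries the factor. If L-ELAPE stays at 6.1% but has the 15% prevalence, r₀ = 6.1/1.30 = 4.7%. L-ISR then shows 4.7 × 1.90 = 8.9%, a false 2.8 points against L-ISR.

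Other assumptions, with L-ELAPE held at 6.1% and the factor commoner there:
- RR 2, 30% against 50%: 6.1/1.5 × 1.3 = 5.3%, a difference of 0.8 points.
- RR 4, 10% against 60%: 6.1/2.8 × 1.3 = 2.8%, a difference of 3.3 points.

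**QoL: unadjusted t test at 72 per group, no true effect**

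Let b be the confounding bias in SD units. The standard error is √(2/72) = 0.167. The error rate of a nominal two-sided 5% test is 1 − Φ(1.96 − b/0.167) + Φ(−1.96 − b/0.167).

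| b (assumed) | 0.1 | 0.2 | 0.3 | 0.4 | 0.5 |
|---|---|---|---|---|---|
| Actual error | 9% | 22% | 44% | 67% | 85% |

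For b = 0.2 this is 1 − Φ(0.76) + Φ(−3.16) = 22%.

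**The case against.** **This is a condensed article and the analysis plan is not shown.** Covariate lists and propensity models are often left to that plan, and naming t and chi-square tests does not say that they are the only analysis. This carries weight: an unseen plan may add adjustment. But the article is not silent here. It assigns a test to each data type and names its multivariable method, and that method does not fit the outcomes in question.

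**The eligibility criteria narrow the case mix.** Tumours lie within 5 cm of the anal verge, are cT1–3 without adjacent invasion, and patients are ASA I–III and ECOG 0–2. This limits imbalance but does not remove it, since tumour height, stage, age and fitness still vary within those bounds.

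**A reader might infer more than the text supports.** It is tempting to state as fact that the groups will differ in tumour height, stage, response, age and baseline function, or that less responsive tumours will go to L-ELAPE and tilt the result towards non-inferiority for L-ISR. No section reports this. Section 2.6 explains why centres would not randomise; it does not say that surgeons allocate by tumour features in this trial. The opposite selection would bias the result the other way.

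**The 2-point benchmark is an assumed true difference, not a margin.** The text gives no margin, and the formula figure is not shown. Solving back from 72 per group at one-sided 0.025 and 80% power gives about 14 points if the 2-point deficit is allowed for, 12 if no difference is assumed, and 10 if the deficit enters with the opposite sign. Against margins of that size, a false 1.9 to 3.6 points is a partial distortion and would not decide the result alone.

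**The trial declares itself non-randomised and phase I/II.** That is candid about the design, but it does not make a crude comparison suitable for a non-inferiority claim.

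**Conclusion.** The point holds in this form: section 2.7 states an analysis that leaves confounding by indication uncontrolled for the primary QoL scores and for the incomplete CRM rate used for sizing. It does not extend to the survival outcomes, which the Cox model can adjust.

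Neither the direction nor the size of any bias can be known from the documents. Under the assumed tripling factor at 15% against 45%, the false CRM difference is about 1.9 to 3.6 points depending on the base rate, similar to the 2-point difference the plan assumes. A reader might conclude from the 3.6 alone that the bias would exceed the planned difference. Anchored to the plan's own 6.1% in L-ELAPE, the same scenario gives 1.9, so that conclusion is not supported. For QoL, an assumed bias of 0.2 to 0.3 SD would raise a nominal 5% error to 22% to 44%.

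**What to change.** In section 2.7, before the groups are compared:

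1. Make an adjusted comparison the main analysis for the QoL scores and incomplete CRM.
2. Estimate a propensity score from pre-operative variables that the eligibility screen already requires (distance from anal verge, cT and cN stage, age, ASA, ECOG) plus sex. Add restaging response and operating surgeon where recorded.
3. Name overlap weighting as the single method. The comparison then targets patients for whom either operation was a realistic choice, and the target population is not left open.
4. For QoL scores, use a weighted linear model of the follow-up score that includes the pre-operative score, if it is collected.
5. For CRM, report the weighted risk difference with its confidence interval. About 10 expected events cannot support an outcome model with many covariates.
6. Keep the crude tests as supportive, and state that unmeasured confounding remains.

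**Cost.** Revised wording, a little more analysis work and some loss of precision. As a rough guide, if the covariates explain a share R² of the choice, the number needed is 72/(1 − R²): 80, 90 or 103 per group before dropout for assumed R² of 0.1, 0.2 or 0.3. No readable section confirms that pre-operative questionnaire scores, restaging response or surgeon are recorded. The follow-up table and flow diagram are not shown, so the sponsor should check. If they are not recorded, including them would need new data collection.

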### Monitoring

2.8

#### Ethics and dissemination

2.8.2

Before enrollment of the first patient, the current trial has been approved by the Clinical Research and Biomedical Ethical Committee (CRBEC) of West China Hospital of Sichuan University (WCH IRB 2018–057; May 17, 2018) and also registered at ChiCTR.org (ChiCTR1800017512; August 2, 2018). Written informed consent will be obtained from every patient for acquisition and utilization of anonymized clinical data prior to recruitment. The purpose and process of the research will be introduced in detail to the eligible patients. Only patients who have understood the purpose and risk of the research and signed the informed consent can participate in this trial. This trial will be conducted in accordance with the study protocol and the principles of the Declaration of Helsinki.^[32]^

The current study is funded by Wu Jieping Medical Foundation. All authors declare that there are no conflicts of interest to disclose. The collected data will be stored for 3 years after termination of this study. The information obtained through the data analyses will be published in an academic journal and publicly shared. Before being completely destroyed, data are available from the responsible investigators upon reasonable request and with permission of Chinese Clinical Trial Registry.

## Discussion

3

Currently, the hot issue of the treatment for LRC located within 5 cm from anal verge is still being debated worldwide. The rapid improvement of surgical techniques and devices and universal utilization of preoperative treatment brings not only opportunities to management of LRC but new challenges to overcome. There is much controversy, however, on a new question as to which surgical option is more appropriate for patients with LRC after favorable response to nCRT to obtain better postoperative QoL and survival outcomes.

Although recent reports suggest that ultimate sphincter-preserving procedures, including ISR, may be feasible to cure LRC without compromise of resection margins and subsequent survival outcomes,^[13,33]^ advanced surgical technique is indispensable for ISR to deliver oncologic efficacy. There is a steep learning curve to successfully completing the L-ISR or L-ELAPE operation, including precise knowledge of rectal anatomy and its anomalies, to avert injury to critical adjacent structures. Perineal wound complications will be attached great importance on and biomaterial as a novel alternative will be used for pelvic floor reconstruction in the L-ELAPE group of our study. As for ISR, anastomotic leakage and anastomotic stricture must be taken into further consideration.^[34,35]^ Thus, prophylactic ileostomy will be performed for selected patients with higher risk of anastomotic leakage and digital rectal examination monthly after surgery is necessary in the L-ISR group.

Given the evident psychological and social impact of permanent colostomy required by APE surgeries, ISR was developed to provide a sphincter-preserving alternative.^[36,37]^ However, recent studies have challenged the assumption that global QoL is worse in patients with permanent stomas (eg, ELAPE patients).^[18]^ A matched-pair analysis comparing the long-term functional outcomes and QoL for 2 post-surgical populations indicated that ISR was associated with higher frequency of diarrhea and constipation than APE.^[16]^ Postoperative continence is exactly an important clinical outcome for LRC patient. Therefore, the pros and cons of each procedure will be discussed with patients and their families before decision making in our study. Psychological guidance, incontinence and stoma care education, and instruction of sphincter exercises will be added into the follow-up for both groups.

To our knowledge, this is the first prospective clinical controlled trial to evaluate postoperative QoL and efficacy for patients with LRC after favorable long-course nCRT. We will conduct the trial with high quality control and publish the result which is expected to provide new evidence for a more detailed individualized treatment guideline for LRC.
